### Randomization and allocation

The study follows a randomized waitlist-controlled design:Experimental group: standard rehabilitation care plus music-based intervention during the first intervention phase.Control/waitlist group: standard rehabilitation care during the first intervention phase, followed by music-based intervention after completion of the experimental group intervention.

Random allocation will take place after obtaining informed consent.

The selection, randomization, and follow-up process will be represented in a flow diagram (Figure 1), consistent with recommendations for waitlist-controlled trials. Randomization will be generated by a member of the research team using simple randomization software. If recruitment is extended to additional centers, randomization will be monitored across centers to maintain balance between groups within each recruitment phase. Group allocation will be concealed until the point of assignment to ensure masking of the sequence.

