### Study design

This is a prospective, phased, randomized waitlist-controlled intervention study with a parallel-group design, aimed primarily at evaluating the effects of the intervention on motor function. Upper-limb motor function will be assessed as a secondary motor outcome, while executive functioning and stroke-specific quality of life will be examined as exploratory outcomes. Participants will be randomly allocated to either an experimental group or a control/waitlist group.

The study will be implemented in successive recruitment phases. The first phase will be conducted in a single outpatient neurological rehabilitation center in the Community of Madrid, Spain, and subsequent phases will extend recruitment to additional outpatient neurological rehabilitation centers within the Community of Madrid until the required total sample size is achieved.

In the first recruitment phase, approximately 24 participants are expected to be included, with 12 participants allocated to each group. Recruitment will then continue in subsequent phases across additional centers, maintaining the same eligibility criteria, intervention protocol, assessment schedule, randomization procedures, and outcome measures, until the planned sample of 76 participants is reached.

Two groups will undergo the same overall rehabilitation process. Over a total of 5 weeks (two sessions per week), the experimental group will receive their standard rehabilitation care complemented by a program of music-based activities. The control/waitlist group will receive only standard rehabilitation care during the first 5-week intervention period and will subsequently undergo the music-based program after the experimental group has completed it, thereby effectively switching their roles.

This design ensures that all participants benefit from the intervention while allowing temporal comparison between the groups. This structure is consistent with previous studies of similar music-based rehabilitation programs and supports ethical rigor by ensuring that all participants receive a potentially beneficial intervention.

All participants will be assessed at baseline (week 0), after 5 weeks (post-intervention), and again at 10 weeks (after crossover). A 3-month follow-up will be conducted to explore the maintenance of potential effects.

The study has been preregistered in OSF Registries.^1^ This record is reported as an open science preregistration and is not presented as a clinical trial registry.

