### Sample size

The sample size was calculated following recommendations for comparing two means in intervention studies (23). As the Fugl-Meyer Assessment (FMA) was the main outcome, change in this measure was selected as the primary criterion. Following previous research (24), the minimal difference in scores used to detect between-group differences in motor improvement was 4, assuming a standard deviation of 12. Using a two-tailed t-test for the difference between means with 80% power and a 5% level of significance, the sample size required was 70 participants, with 35 per group. Considering a dropout rate of 10%, the final required sample size was estimated at 76 participants, with 38 per group.

Given the specificity of the target population and the outpatient rehabilitation context, recruitment will be conducted in successive phases. The first recruitment phase, conducted in a single center, is expected to include approximately 24 eligible and recruitable participants, with 12 participants per group. Subsequent phases will include additional outpatient neurological rehabilitation centers in the Community of Madrid until the total required sample size of 76 participants is reached. Based on the projected recruitment capacity across participating centers, completion of recruitment is expected within approximately 1 year.

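### Simple randomization does not secure the balance within phases that the protocol says it will maintain by monitoring, and the primary model has no centre term

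*Protocol article*

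**What the plan says.** The section on randomization and allocation fixes the method: "Randomization will be generated by a member of the research team using simple randomization software". For the case that further centres join, it adds that "randomization will be monitored across centers to maintain balance between groups within each recruitment phase". It then states the aim of concealment: "Group allocation will be concealed until the point of assignment to ensure masking of the sequence". The article names no blocks, strata or minimization, and no action to follow if imbalance is seen. Study design and Recruitment both carry the same randomization procedures to every centre and phase.

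Equal arms appear in two places. For the first, single-centre phase, Study design says that "approximately 24 participants are expected to be included, with 12 participants allocated to each group". For the whole trial, Sample size says that "the final required sample size was estimated at 76 participants, with 38 per group".

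Three other sections bear on the point:

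- **Blinding:** participants, providers and outcome assessors are unblinded; only the statistician is blinded.
- **Standard rehabilitation care:** usual care follows each centre's own practice. The first centre's weekly timetable is described; for later centres, the frequency and mix of therapies are recorded.
- **Statistical analysis:** the model has time, group and their interaction, time since stroke as a covariate, and a random intercept. It has no centre or phase term.

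**The concern.** Simple randomization treats each assignment as independent of those before it, so nothing in the method pulls the arms together, in a phase or overall. A promise to maintain balance therefore needs something that the named method does not contain. Two outcomes are possible if the text is followed as written.

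- **Someone acts on the running tally.** Later assignments then depend on earlier ones through a decision, not through a pre-set sequence. Staff in an unblinded trial can see past assignments, so those who know the tally could anticipate the next one. That opens the way to selection bias, which analysis cannot repair, and it works against the concealment stated in the same paragraph.
- **Nobody acts.** Arm may then be unevenly spread across centres with different standard care, and the stated primary model does not adjust for it.

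**Working it through.** **Inputs.** Phase 1 has about 24 participants and the trial has 76 (Study design, Sample size), which leaves 76 − 24 = 52 for later phases. Allocation is 1:1, as implied by 12/12 and 38/38. The calculation assumes that participants are allocated independently with probability 0.5; the article does not state this, but it is what simple randomization ordinarily means.

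**1. The plan's own splits.** 24/2 = 12 and 76/2 = 38. These are the expected values of a 1:1 scheme, so they are right as expectations.

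**2. How often simple randomization gives them.** With X ~ Binomial(n, 0.5), P(X = n/2) = C(n, n/2)/2ⁿ. For n = 24 this is 2,704,156/16,777,216 = 0.161.

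| n | Exactly equal | Larger imbalances | Central 95% range per arm |
|---|---|---|---|
| 24 (phase 1) | 16.1% | 15:9 or worse 30.7%; 16:8 or worse 15.2% | 7 to 17 |
| 52 (all later phases together) | 11.0% | 31:21 or worse 21.2% | 19 to 33 |
| 76 (whole trial) | 9.1% | 43:33 or worse 30.2%; 46:30 or worse 8.5% | 29 to 47 |

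The article does not give the number or size of later phases and centres. If a later phase also had 24 participants (an assumption), the first row would apply to it.

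**3. What unequal arms cost in power.** The effective size per arm is 2·n₁·n₂/(n₁ + n₂). A 34/42 split gives 2 × 34 × 42/76 = 37.6 against 38. The edge of the 95% range, 29/47, gives 2 × 29 × 47/76 = 35.9.

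For power, an effect size is needed. The stated inputs (a difference that "was 4, assuming a standard deviation of 12") do not give 35 per group: n = 2 × 12² × (1.960 + 0.842)²/4² ≈ 142 per group. That is a separate matter, so the power check was run at both effect sizes: 4/12 = 0.333 as stated, and 4/6 = 0.667, which roughly fits 35 per group. Power was averaged over the binomial split:

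| N | Effect size | Balanced | Average under simple randomization | Loss (points) |
|---|---|---|---|---|
| 70 | 0.667 | 78.5% | 77.9% | 0.6 |
| 76 | 0.667 | 81.8% | 81.3% | 0.5 |
| 70 | 0.333 | 28.0% | 27.6% | 0.3 |

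At N = 70 and effect size 0.667, a 27/43 split still has 76.3% power. Power is therefore not the issue.

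**4. The two sentences side by side.** The first names a method without memory. The second promises an outcome that depends on memory. Both can be true only if allocations are influenced by the tally, or if a restricted scheme is used that the article does not name. In the first case allocation integrity suffers; in the second the stated method is wrong.

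**5. What permuted blocks would give.** Arms are equal whenever blocks are complete, and the difference within a stratum is at most half a block: 2 for a block of 4 (an assumed size).

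**The case against.** A reader might infer three stronger things, and the documents support none of them.

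- **That the team plans to steer allocations.** The text speaks only of monitoring. It does not say that any assignment will be changed, and it states concealment in the next sentence. The authors may have a restricted scheme in mind, or may use the word simple to describe the software. The clause is also conditional on further centres joining, so the figures for 24 say nothing about steering in phase 1.
- **That simple randomization cannot produce the stated arms.** It can; it does not guarantee them. The phase 1 split is given as approximate and expected, and 38 per group is a planning figure. Missing an exact split is ordinary for any simple 1:1 scheme. If a whole cohort were allocated together by drawing 12 of 24, the split would be exact and there would be no next assignment to guess. The article does not describe such a draw, but it does not exclude one.
- **That the trial loses power.** One arm falls below 35 before dropout in 42% of draws at n = 76, which sounds serious beside "the sample size required was 70 participants, with 35 per group". Step 3 of the working shows that the loss is under one point on average.

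It is also fair to say that chance imbalance between centres is not systematic bias, that each participant's therapy is logged, and that Limitations allows for adjustment in the analysis where suitable. But that allowance is not tied to the primary model, which is fully listed without centre. Finally, who prepares the list and how it is released may well stand in a fuller document, so their absence here is not part of this point. What remains is that the article fixes a method and attaches to it a goal that the method does not serve.

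**Conclusion.** The point holds as an internal inconsistency in the section on randomization and allocation. Simple randomization does not secure balance: under independent allocation, an exact 12/12 is missed in about 84% of draws and 15:9 or worse occurs in about 31%. The monitoring clause could be honoured under that method only by acting on the running tally, although the article does not say that this will happen. If it is not honoured, centre imbalance enters a primary model without a centre term. The consequence is for allocation integrity and centre comparability, not for power. The size of any imbalance by centre cannot be given, because the number and size of later centres are not stated. This should be corrected before the first participant is allocated.

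**What to change.** Replace simple randomization with one pre-specified, computer-generated scheme: permuted blocks of randomly varying size, stratified by centre (or by centre and phase cohort), fixed before each centre opens. Delete the clause on monitoring to maintain balance, since the scheme then does that work. Add the stratification factor to the primary mixed model. Because the treatment effect is read from the group-by-time interaction, and differing standard care would act on change over time, also state whether the factor enters with its own interaction with time.

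Recruitment has not started (Study status), so the cost is a software setting, a rewritten paragraph and one more model term. The drawback is slightly more predictability within blocks than under simple randomization, which random block sizes limit. With many small centres, incomplete blocks would leave small residual differences, each at most half a block.

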**Figure 1 fig1:**
[figure not shown]
Flow diagram of participant screening, recruitment, randomization, intervention, crossover, and follow-up across recruitment phases.

### Blinding

Due to the nature of the music-based intervention, neither participants nor the professionals delivering the intervention can be blinded. Outcome assessors will not be blinded due to logistical reasons. To minimize potential bias, standardized assessment procedures will be strictly followed, and assessors will receive prior training in the administration of all outcome measures to ensure consistency in data collection. In addition, objective and widely validated instruments will be used whenever possible.

The statistician will not be involved in intervention delivery or outcome assessment and will be blinded to group allocation during the primary analysis. Groups will be coded as Group A and Group B until the primary analysis has been completed to reduce potential analytical bias.

### Interventions

#### Groups

Two parallel groups will be formed: the experimental group and the control/waitlist group.

#### Standard rehabilitation care

Post-stroke rehabilitation typically addresses a range of sequelae affecting motor function, communication, cognition, and activities of daily living. Common impairments include hemiparesis, coordination deficits, language disturbances, and executive dysfunction, which require multidisciplinary intervention to support functional recovery and independence.

All participants will continue their prescribed standard rehabilitation care. This typically includes a combination of physiotherapy, occupational therapy, speech and language therapy, and, when indicated, neuropsychological intervention, as prescribed in the clinical setting.

In the outpatient rehabilitation settings participating in the study, standard rehabilitation care will be delivered according to each center’s usual clinical practice. In the first recruitment center, patients typically attend the rehabilitation center from Monday to Friday between 9:00 and 16:30 to receive individualized and group therapy sessions. In subsequent centers, the frequency and combination of therapies will be recorded according to each participant’s clinical needs and rehabilitation plan.

During the study period, participants will be required to maintain a stable rehabilitation schedule to minimize variability. To ensure comparability between groups, detailed information on the type of therapy, frequency, and session duration will be systematically recorded for each participant at baseline and monitored throughout the intervention using a standardized log. Any relevant changes in rehabilitation intensity or type of therapy will be documented and considered in the interpretation of the results.

This approach allows the study to reflect real-world clinical practice while maintaining sufficient methodological control over conventional treatment exposure.

Participants will also continue receiving their usual medical care, including any prescribed pharmacological treatments, which will not be modified as part of the study. Any relevant changes in medication during the study period will be recorded.

#### Music-based intervention

The intervention is defined as a structured music-based intervention rather than a formal music therapy intervention. This terminology was selected because the program will be delivered by a healthcare professional with formal musical training and experience in rehabilitation contexts, but not by a formally credentialed music therapist. Accordingly, the intervention is not presented as clinical music therapy and does not claim to replace treatment delivered by a qualified music therapist. Instead, it is conceived as a standardized, rehabilitation-oriented, music-based program designed to complement usual post-stroke rehabilitation care.

The intervention is based on a neuroscience-informed and integrative music-based approach, combining rhythm-based, instrumental, and structured musical activities to primarily support motor rehabilitation while incorporating cognitive and emotional components. Activities involving rhythmic sequencing, improvisation, and structured musical interaction are designed to engage executive functions, such as cognitive flexibility, working memory, and inhibitory control. Cognitive neuroscience has indicated that musical rhythm and structured auditory–motor activities recruit frontal and frontoparietal networks involved in executive functioning (10, 20, 21). These activities are included to increase cognitive engagement during motor and musical tasks rather than to constitute a stand-alone cognitive rehabilitation program.

The intervention is not intended to replicate standardized neurologic music therapy (NMT) protocols, but to adapt selected rhythm- and instrument-based principles to the aims and constraints of an outpatient post-stroke rehabilitation setting. The rhythmic components are informed by rhythmic auditory stimulation (RAS), particularly the use of an external, predictable beat to support movement timing, synchronization, and coordination (25). In this protocol, these principles are mainly adapted to seated upper-limb and whole-body coordination tasks, rather than to formal gait training. Instrument-based motor activities are conceptually related to therapeutic instrumental music performance (TIMP), which is defined in the updated second edition of the Handbook of Neurologic Music Therapy as a technique that uses structured musical instrument playing to facilitate upper-limb movement, coordination, and functional motor recovery in neurological populations (26). In the present intervention, TIMP-related principles are applied through goal-directed percussion and melodic-instrument tasks, with the instrument position, movement amplitude, rhythmic complexity, and level of cueing adapted to each participant’s motor abilities and fatigue.

The program was designed as an integrative and flexible intervention adapted to an outpatient rehabilitation setting, allowing adjustment of task complexity, level of motor engagement, and cognitive demands according to participants’ functional abilities and progression throughout the intervention. The intervention will be delivered by a nurse with experience in the management of stroke patients and formal professional musical training, with support from a professional experienced in post-stroke rehabilitation. Intervention facilitators will receive specific training in the study protocol before the start of the intervention at each participating center, including session structure, safety procedures, adaptation criteria, documentation of participant responses, and fidelity monitoring.

Previous studies on music-based interventions, neurologic music therapy, and music-supported rehabilitation in stroke populations report considerable heterogeneity in the intervention duration and intensity, with no clear consensus on the optimal dosage (13, 17). However, many studies conducted in chronic stroke populations have implemented structured multi-session interventions with frequencies ranging from one to three sessions per week over several weeks (22, 27), providing a general reference framework for intervention design. Accordingly, the intervention dose (10 sessions delivered twice weekly over 5 weeks, including 6 individual and 4 group sessions) was determined to be consistent with commonly used intervention ranges reported in previous music-based and neurologic rehabilitation studies (13, 17, 22, 27), while also considering feasibility within a real-world outpatient rehabilitation setting. This schedule was selected to balance intervention intensity, participant burden, and adherence while allowing evaluation of participant response.

The intervention has been described in accordance with recommendations for reporting music-based interventions, including the original Reporting Guidelines for Music-Based Interventions (RG-MBI) recommendations and the updated RG-MBI checklist (28, 29). The description specifies the theoretical rationale, intervention components, delivery format, intervention setting, musical materials and parameters, facilitator training, tailoring and progression rules, and treatment fidelity procedures.

This structured format enables standardized delivery while maintaining flexibility for individual adaptation.

Musical parameters, including tempo, rhythmic complexity, movement amplitude, instrument type, and level of facilitator cueing, will be adapted according to participants’ motor capacity, fatigue, comprehension, and emotional response. Tasks will begin at a level that allows successful participation and will progress by increasing rhythmic complexity, tempo, task duration, bilateral involvement, range of movement, memory load, or degree of independence. Task difficulty will be reduced if participants show excessive fatigue, frustration, loss of postural control, inability to follow instructions, or emotional discomfort. Treatment fidelity will be supported through facilitator training, use of the standardized session protocol, and completion of a session checklist documenting attendance, activities delivered, adaptations made, participant engagement, adverse events, and deviations from the protocol.

Session checklists will be reviewed periodically by the research team to monitor adherence to the protocol and identify deviations requiring corrective action.

The intervention consists of a 10-session structured program delivered twice per week over 5 weeks, including 6 individual sessions and 4 group-based sessions.Individual sessions (30–40 min): Focused on evaluation and individualized work on motor engagement, rhythmic participation, and emotional regulation.Group sessions (45 min): Conducted collectively with all participants, focused on social interaction, motor coordination, and emotional support.

These group-based and receptive components are informed by music therapy and music-based rehabilitation approaches commonly used to support emotional regulation, social interaction, and quality of life in rehabilitation populations. Group singing, shared rhythmic activities, and guided listening are consistent with rehabilitation-oriented music-based frameworks that emphasize emotional expression, social engagement, and patient-centered rehabilitation (6, 7).

